#### Statistical analysis

Statistical analysis will be performed by an independent external statistician ([name]). This study is designed as an explorative study to provide data for future confirmatory studies. The main outcome variable (area under the curve, AUC) for each biomarker will be analyzed using intra-operative ischemia as the only explanatory variable in the two groups. No corrections will be made for multiplicity. A difference of ≥ 2 standard deviations (SD) in the main outcome variable is considered to be a statistically relevant effect. The alpha level is set at 0.05 %. The 95 % confidence intervals for the differences will be calculated.

No a priori empirical evidence suggests which of the six chosen biomarkers would be the ideal single primary outcome, but to define the sample size, we allocated the AUC of S100 as the primary outcome. Power analysis aiming to detect a difference of more than two SD in the primary outcome between the groups would require a sample size of *n* = 16σ2/d2 for a two-sided α = 0.05 and 1-β = 0.8 [85]. *N* = 4 patients per group would permit a difference of ≥ 2 SD in serum biomarker levels to be detected in the study population. Assuming that only one in five patients will sustain cerebral ischemia during aneurysm treatment, this would require a sample of *n* = 20 patients per group. Additional 20 % (*n* = 4 patients) per group will be included for unexpected dropouts, unexpected low rates of intra-interventional ischemia or unexpected loss to follow-up. This would require a total study population of *n* = 48 patients (*n* = 24 per group).

All statistical analysis will be performed on an intention-to-treat basis and per protocol. Standard methods of exploratory data analysis will be used for group comparison. Quantitative parameters will be tested for normality and compared using the *t* test or compared with the Mann–Whitney *U* test for non-normally distributed data. Qualitative parameters will be compared using the chi-squared test or Fisher’s test. Group differences for the main outcome variable will be compared using the two-sided *t* test for independent groups or the Mann–Whitney *U* test, as appropriate. Secondary outcome parameters will be compared using the Mann–Whitney *U* test for quantitative data and the chi-squared or Fisher's test for dichotomized outcome data.

Preplanned subgroup analyses include an analysis stratified by aneurysm treatment technique (microsurgical or endovascular) and by anesthetic regimen (with or without propofol).

Missing data for biomarker serum values (for example, due to hemolytic probes) will be handled using a statistical model and the maximum likelihood method, in which estimates and standard errors are based on the likelihood function given in the observed data. Missing imaging data (for example, inability to investigate by MRI during the first 2 postoperative days) will be replaced by calculating the number and volume of areas assumed to be due to ischemia on the basis of CT scans (if available)

The SAS software package V9.1 will be used for statistical analysis.

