### Why include two different procedures in the study protocol?

We included both procedures - microsurgical clipping and endovascular coil occlusion of intracranial aneurysms - because both may induce focal cerebral ischemia (ischemia to one defined cerebral vascular territory) and because both may lead to local endothelial damage. Both procedures carry a comparable risk to induce focal cerebral ischemia.

The difference is that, in endovascular procedures, the source of ischemia is inside the vessel and in direct contact with the endothelium and the bloodstream, whereas in microsurgical clipping, the ischemia-inducing agent is outside the vessel lumen. This might be a drawback in the study design but could also increase the external validity of this study. Other possible technical confounders in a study of this type that defeat standardization include but are not limited to (1) a different duration of vessel occlusion between the study individuals, (2) a lack of possibility to differentiate between complete and incomplete vessel occlusion, (3) the impossibility to control for collateralization of the occluded vascular territory, and (4) the fact that some patients will undergo repetitive occlusion periods and others a singular occlusive period as dictated by clinical necessity.

The goal of the RIPAT study is to investigate whether remote ischemic preconditioning during the elective treatment of intracranial aneurysms reduces the occurrence of ischemic damage as measured by serum biomarker determination, neuroimaging, and clinical, as well as neuropsychological, examination.

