#### Remote ischemic preconditioning (RIPC) and sham preconditioning (SPC)

Study patients will be randomly assigned to either the preconditioning group (Group A, treatment group) or the control group (Group B, sham preconditioning) on opening a sealed envelope containing the group assignation after anesthesia is induced in the induction room. In both RIPC and SPC, a standard blood pressure cuff is fixed on the patient’s upper arm. Care will be taken to ensure that the blood-pressure cuff is adequate to accommodate the patient’s arm [77]. In Group A, RIPC consists of cuff inflation to 200 mmHg for 3 x 5 min alternating with 5 min of intermittent reperfusion by complete cuff deflation. In Group B, maximum cuff inflation pressure is limited to 10 mmHg for 3 x 5 min alternating with 5 min of complete cuff deflation.

RIPC and SPC will be performed by the anesthesiologist aided by a second, unblinded member of the study team after the induction of general anesthesia and prior to definitive patient positioning for the intervention. These two members of the team are not involved in the intra-interventional decisions concerning deliberate ischemia and are blinded for outcome analysis. Standard operation procedures (SOP) describing the preconditioning procedure are available to all investigators (see Additional file 1: Supplementary material). A written checklist must be completed by those performing the preconditioning to ensure protocol adherence (see Additional file 1: Supplementary material).

Adverse events or unintended effects of the trial intervention will be noted in the preconditioning protocol and communicated to those performing the subsequent aneurysm treatment. The decision to abort the aneurysm treatment procedure in such a situation will be made by the surgeon or the endovascular therapist after conferring with the principal investigator. Patients with a complication will be managed in a manner appropriate to the situation and informed thereof after recovery from anesthesia.

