#### Aneurysm treatment

Treatment of intracranial aneurysms will consist of either microsurgical clipping or endovascular coiling under general anesthesia following standard methods. All events that could possibly be associated with ischemia, including a drop or deliberate reduction in the systemic blood pressure of more than 20 % of the prior systolic blood pressure lasting more than 3 min and every deliberate or unintentional vessel occlusion during the procedure will be recorded by the anesthesiologist. All injuries and unintended effects associated with the preconditioning procedure or the aneurysm treatment will be registered.

The anesthetic protocol is not prespecified. We expect that the majority of patients will receive total intravenous anesthesia (TIVA) that includes propofol because this is the standard anesthesiologic regimen in our neurosurgical patients. However, the anesthesiologist is free to use the protocol that he/she thinks is the most appropriate. Different interventions will not require different anesthetic protocols.

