#### Randomization

The Center for Statistical Consulting and Continuing Education (CSCCE) at UMIT (University for Health Sciences, Medical Informatics and Technology) generated the random allocation sequence using the PLAN procedure in the SAS statistical package V.9.1. Participants were randomized 1:1 to either the preconditioning group or the sham group using block randomization with a block size of four at a time and a random-block sequence. Assignment of the study subjects was documented in a randomization schedule. Sequentially numbered sealed opaque envelopes containing group allocation for each patient were prepared using the random allocation sequence by a statistician not involved in patient treatment. Envelopes will be opened by one of the unblinded members of the study group (see above) after induction of anesthesia.

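### The main analysis is described in two unreconciled ways, one resting on a post-randomisation event, and the sample size fits only that one

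*Protocol article*

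**What the plan says.** All places are in the protocol article.

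- **Statistical analysis, first paragraph.** The main outcome, the AUC of each biomarker, "will be analyzed using intra-operative ischemia as the only explanatory variable in the two groups".
- **Statistical analysis, third paragraph.** "Group differences for the main outcome variable will be compared using the two-sided" t test for independent groups, or the Mann–Whitney U test. The same paragraph states: "All statistical analysis will be performed on an intention-to-treat basis and per protocol".
- **Statistical analysis, second paragraph.** The size starts from 4 patients per group for a 2 SD difference. It is raised to 20 because one patient in five is assumed to sustain ischemia, and to 24 by a 20 % reserve. Part of that reserve is meant for a lower ischemia rate than expected.
- **Order of events.** Randomization section: "Envelopes will be opened by one of the unblinded members of the study group (see above) after induction of anesthesia". The cuff procedure follows "after the induction of general anesthesia and prior to definitive patient positioning for the intervention". Under Aneurysm treatment, "every deliberate or unintentional vessel occlusion during the procedure will be recorded by the anesthesiologist", as are larger drops in blood pressure.
- **Aim** (end of the section on including two procedures). To find out whether RIPC "reduces the occurrence of ischemic damage as measured by serum biomarker determination, neuroimaging" and clinical and neuropsychological examination.

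**The concern.** The first description makes ischemia the sole explanatory variable. Taken literally, allocation is not in the model, and the result is an association between ischemia and biomarker level. The second description is an ordinary comparison of the randomised arms. These are different analyses of the same outcome, and nothing in the section ranks them.

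Ischemia during the procedure comes after allocation and after the cuff procedure. If the first description means comparing arms among ischemic patients, the comparison keeps the protection of randomisation only if RIPC does not alter who is counted as ischemic. The section does not settle whether ischemia here means tissue injury, which RIPC is intended to reduce, or logged occlusions and pressure drops.

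Two things are at stake. An analyst could follow either description and report a different quantity as the main result. And the stated sample size supports one description but not the other. The Discussion ties the planning of later trials to whether a primary outcome differs significantly between groups, so the contrast has to be identifiable even in an exploratory trial.

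**Working it through.** **1. Reproduce the plan's size.** Inputs from Statistical analysis: d = 2σ, two-sided α = 0.05, power 0.80, ischemia rate 0.20, reserve 20 %.

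- n = 16σ²/d² = 16/4 = 4 per group. The unrounded normal formula, 2 × (1.960 + 0.842)²/2², gives 3.92, which rounds up to 4.
- 4/0.20 = 20; 20 × 1.2 = 24 per group; 48 in total.

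The figures reproduce. Dividing 4 by the ischemia rate makes sense only if the 4 are ischemic patients, so the size belongs to a comparison within the ischemic subgroup.

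**2. How well that size serves the subgroup comparison.**

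- With exactly 4 ischemic patients per arm, power at 2 SD is 81 % by the normal approximation but about 66 % by the noncentral t (6 degrees of freedom, noncentrality 2 × √(4/2) = 2.83). With 5 per arm it is about 79 %.
- At a 20 % rate, the binomial chance that one arm has at least 4 ischemic patients is 0.589 with 20 per arm and 0.736 with 24. For both arms: 0.589² = 0.35 and 0.736² = 0.54.

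**3. The candidate analyses target different quantities.** Illustrative assumption: ischemia in 20 % of each arm, ischemia adds 2 SD to AUC, and RIPC abolishes that rise.

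| Analysis | Result |
|---|---|
| AUC on ischemia alone, arms pooled | slope about 1.0 SD, no RIPC contrast |
| Arms compared, all randomised patients | 0.20 × (−2) = −0.4 SD |
| Arms compared, ischemic patients only | −2.0 SD |

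**4. Power of 24 per group for the all-patient comparison.** Assumption: the 2 SD effect exists only in ischemic patients. The difference is then 2p SD at ischemia rate p, and the noncentrality is 2p × √(24/2). The mixture of ischemic and non-ischemic patients also widens the control arm: its variance is 1 + 4p(1 − p), and the average SD of the two arms is √[(1 + 1 + 4p(1 − p))/2]. The 60 % rate is the upper figure for endovascular procedures in the section on why these patients are studied.

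| p | Difference | Power, SD = 1 (t / normal) | Average SD with mixture | Power with mixture SD (t) |
|---|---|---|---|---|
| 0.20 | 0.4 SD | 27 % / 28 % | √1.32 = 1.149 | 22 % |
| 0.60 | 1.2 SD | 98 % / 99 % | √1.48 = 1.217 | 92 % |

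Normal check at p = 0.20: 0.4 × √12 = 1.386, and Φ(1.386 − 1.960) = 0.28. At that rate 80 % power would need about 99 per group, or about 130 with the mixture SD. If instead 2 SD is the difference across all randomised patients, power at 24 per group exceeds 99 %.

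**5. Selection when conditioning on ischemia.** Illustration for one meaning of the word only. Suppose ischemia is the top 20 % of a standard normal severity that is also the outcome, and RIPC lowers severity by 0.5 SD in everyone. The RIPC-arm rate falls to 9 %. The mean among ischemic controls is 1.400 and among ischemic RIPC patients 1.305, a difference of 0.095 SD instead of 0.50. If ischemia means occlusions or pressure drops whose frequency RIPC does not change, this bias does not arise.

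**The case against.** The strongest reply is that the plan does contain a proper randomised comparison. The t test or Mann–Whitney sentence, the intention-to-treat statement and the power wording about a difference between groups all point that way. This stands. A reader might infer from the first description that the trial never estimates the RIPC effect, and the later sentence rules that out. The phrase about the two groups is also ambiguous: it may mean that ischemia-related AUC is compared between arms, or that no covariate other than ischemia is used. What remains is that the section does not choose between the two descriptions.

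A reader might also take the illustration in step 5, a loss of about 80 % of the effect, as the size of the problem. The documents do not support that. It needs ischemia to be a cut-off on the outcome's own severity, and the plan states no such definition.

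A third inference would be that the ischemia log is kept by an unblinded person. The section on the cuff procedure has the anesthesiologist perform it, and Aneurysm treatment has the anesthesiologist record events. But the Blinding section says that trial data are collected by staff unaware of allocation and that the unblinded members take no part in patient treatment. Whether the two anesthesiologists are the same person is not settled, so the point cannot be asserted.

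Finally, the trial is explicitly exploratory. That limits the consequence but does not reconcile the two sentences.

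**Conclusion.** The point holds as a contradiction within one section. Two descriptions of the main analysis stand side by side without a ranking, and the sample size fits only the ischemia-conditional one. The literal form of the first description does not estimate the RIPC effect. Its arm-comparison form can be biased if RIPC changes who is classed as ischemic, by an amount that cannot be fixed from the documents because ischemia is not defined for this purpose.

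The size that can be given concerns power. For the all-patient comparison, 24 per group gives about 27–28 % at a 20 % ischemia rate (about 22 % if the mixture widens the SD) and about 92–98 % at 60 %. Both rest on the assumptions that the 2 SD effect is confined to ischemic patients and that two-sided α is 0.05, as in the sample-size paragraph.

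**What to change.** Three changes in the Statistical analysis section:

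1. Replace the first description with wording such as: *The primary analysis compares AUC between the randomised groups in all randomised patients; allocated group is the explanatory variable.*
2. Move intra-operative ischemia to a labelled exploratory analysis (for example group by ischemia, reported descriptively). Define ischemia for that purpose, and state that it is observed after randomisation and is not a test of RIPC efficacy.
3. Restate the power of 24 per group for the all-patient comparison, giving the assumed ischemia rate and whether the 2 SD effect applies to all patients or only to those with ischemia.

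The cost is a revised analysis paragraph and a revised power statement, with no new data or patients. The downside is that the stated power may look less favourable. Making the first change without the third would leave the plan inconsistent.

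### The analysis alpha is printed as 0.05 % (0.0005), which contradicts the two-sided 0.05 used for sizing and the planned 95 % confidence intervals

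*Protocol article*

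**What the plan says.** All the relevant statements stand in the protocol article, under Statistics, Statistical analysis.

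- Significance level for the analysis: "The alpha level is set at 0.05", with a percent sign after the figure.
- Intervals, in the next sentence: "The 95 % confidence intervals for the differences will be calculated".
- Level and power used for sizing, one paragraph later: "for a two-sided α = 0.05 and 1-β = 0.8".
- Size of effect, in the sentence just before the alpha sentence: "A difference of ≥ 2 standard deviations (SD) in the main outcome variable is considered to be a statistically relevant effect".
- The same 2 SD in the sizing: "Power analysis aiming to detect a difference of more than two SD in the primary outcome between the groups".

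The section also rules out any multiplicity correction. It names a two-sided t test or a Mann–Whitney U test for the main outcome.

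**The concern.** The sentence that sets the significance level for the analysis disagrees with two other statements in its own section. Taken literally, 0.05 % is 0.0005. That level pairs with 99.95 % intervals, not 95 % ones, and with a much larger trial than the one planned. It cannot be an alpha adjusted for six biomarkers, because the section says that no such correction is made.

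At stake is how a result is labelled. The Discussion makes the planning of later trials depend on whether a primary outcome parameter differs significantly between the groups. With two levels in print, a moderate difference could be reported as significant or not, and either report could cite the protocol.

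A second, smaller point is the wording of the 2 SD sentence. It stands in the analysis paragraph and says that such a difference "in the main outcome variable is considered to be a statistically relevant effect". This blurs the difference that the trial is sized to detect with the criterion by which a result is judged.

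**Working it through.** **Inputs, all from Statistical analysis unless noted.** Two-sided α = 0.05 and power 0.80 for sizing; d = 2 SD; n = 16σ²/d² per group; ischemia in one of five patients; 20 % added; 24 per group. Allocation is 1:1 (Randomization).

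**1. Reproduce the plan's figure at α = 0.05.**
- The plan's formula: 16 / 2² = 4.0 per group.
- The 16 is itself a rounded constant for this alpha and power: 2 × (1.960 + 0.842)² = 15.70, and 15.70 / 4 = 3.92, rounded up to 4.
- 4 × 5 = 20; 20 × 1.2 = 24 per group; 48 in total. This matches the plan.

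**2. Repeat at α = 0.0005.**
- The normal quantile rises from 1.960 to 3.481, so the constant becomes 2 × (3.481 + 0.842)² = 37.37.
- 37.37 / 4 = 9.34, rounded up to 10 per group.
- 10 × 5 = 50; 50 × 1.2 = 60 per group; 120 in total. This does not match the plan.

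The stated sample size therefore belongs to 0.05 and not to 0.0005.

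**3. Match the intervals.** 1 − 0.05 = 95 %, as planned. 1 − 0.0005 = 99.95 %, which the plan does not mention.

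**4. Smallest significant observed difference.** For a two-sided t test with n per group, in units of the pooled SD, this is t(1 − α/2, 2n − 2) × √(2/n).

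| n per group | α = 0.05 | α = 0.0005 |
|---|---|---|
| 24 | 2.013 × 0.2887 = 0.58 SD | 3.746 × 0.2887 = 1.08 SD |
| 20 | 2.024 × 0.3162 = 0.64 SD | 3.806 × 0.3162 = 1.20 SD |

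Example at 24 per group: an observed difference of 0.80 SD has a 95 % interval of about 0.80 ± 0.58, or 0.22 to 1.38 SD. The interval excludes zero, yet the same result is not significant at 0.0005. A report that followed both printed sentences would contradict itself.

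**5. Effect on power, like for like.**
- 4 per group, true difference 2 SD, normal approximation (the plan's basis): 80.7 % at 0.05 and 25.7 % at 0.0005.
- The same with the exact t test: 65.7 % and 3.7 %.
- 24 per group at 0.0005, exact t test: about 40 % for a true difference of 1 SD and over 99 % for 2 SD.

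**6. The 2 SD sentence.** The sizing uses d = 2 SD and the analysis paragraph names 2 SD, so the two agree. A conflict arises only if the sentence is read as a threshold for the observed difference. At 24 per group, results from 0.58 to 2 SD would then be significant by the t test but not called relevant. Under such a threshold, a true difference of exactly 2 SD would reach it only about half the time (normal approximation, known SD).

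**The case against.** The strongest reply is that this is a misplaced percent sign which the section itself resolves. The sizing level, the 95 % intervals, the two-sided test and the planned 24 per group all point to 0.05, and nothing in the design depends on 0.0005. The trial is also exploratory and claims no definitive answer. This largely stands: the intended value is hardly in doubt, and no design feature changes. It does not remove the fault, because the faulty sentence is the one that states the alpha for the analysis.

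A reader might infer more than the documents support, in three ways.

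- **That the 2 SD sentence contradicts the sizing, or adds a further success criterion.** It does neither. 2 SD is the sizing's own target, the section names the test that compares the groups, and nowhere does it require an observed difference of 2 SD for a positive result. What remains is loose wording.
- **That a positive result would be nearly impossible at 0.0005.** With 24 per group, power is still over 99 % at the plan's own 2 SD and about 40 % at 1 SD. It becomes very low only for small effects. For 0.4 SD (2 SD diluted by the one-in-five ischemia rate, a figure the plan does not state), it is 1.5 %. Power for that effect is only 27 % at 0.05, so most of the shortfall there is not due to the alpha figure.
- **That power drops from 80 % to 3.7 %.** That sets a normal-approximation figure against an exact one. The fair pairs are those in step 5 of the working.

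**Conclusion.** The point holds for alpha. The printed level is wrong by a factor of 100 against the sizing and the intervals in the same section, and only 0.05 reproduces the stated sample size. The practical consequence is confined to observed differences between 0.58 and 1.08 SD at 24 per group (0.64 to 1.20 SD at 20 per group), whose label depends on the alpha applied. These limits assume the t test, equal variances and complete data; the Mann–Whitney alternative would have its own limits.

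The 2 SD sentence is a secondary matter of wording and involves no arithmetic error. The documents do not support treating it as a decision rule or as a contradiction of the sizing.

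**What to change.** In Statistical analysis, replace the alpha sentence with a statement that tests are two-sided at alpha 0.05 (5 %). In the same edit, reword the 2 SD sentence, or move it to the sample-size paragraph, so that 2 SD is described as the difference assumed for sizing. State that the between-group difference is judged by the two-sided test at 0.05 and reported with its 95 % confidence interval.

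The cost is two sentences. The sample size (24 per group, 48 in total), the tests and the intervals stay as planned.

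### The sample-size argument (4 per group, times five, plus 20 %) does not deliver its stated 80 % power under any analysis that the protocol article describes

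*Protocol article*

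**What the plan says.** All of the sizing is in the protocol article, under *Statistical analysis*.

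- **Outcome.** The authors write that "to define the sample size, we allocated the AUC of S100 as the primary outcome".
- **Step 1.** The required number per group is "16σ2/d2 for a two-sided α = 0.05 and 1-β = 0.8". With a target of 2 SD this gives 4, and the text says that four "patients per group would permit a difference of ≥ 2 SD in serum biomarker levels to be detected in the study population".
- **Step 2.** "Assuming that only one in five patients will sustain cerebral ischemia during aneurysm treatment", the four become 20 per group.
- **Step 3.** A further 20 % (4 per group) covers dropout, a low ischemia rate and loss to follow-up. The result is 24 per group, 48 in total.
- **Analysis.** "All statistical analysis will be performed on an intention-to-treat basis and per protocol". Group differences in the main outcome are tested with a two-sided independent-groups t test or, as appropriate, a Mann–Whitney U test.
- **An ambiguous sentence.** The same section names intra-operative ischemia as the sole explanatory variable for each biomarker's AUC in the two groups. It gives no model and does not restrict the comparison to ischemic patients.

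**The concern.** Step 2 makes sense only if the effect sits in the ischemic patients, because otherwise there is no reason to multiply. The stated test, however, averages over everyone randomised, and four fifths of them are assumed to have no ischemia. Averaging shrinks the group difference in proportion to the ischemia rate p. The required number therefore grows with 1/p², whereas the plan divides by p. Step 1 has a smaller problem of its own: the rule of thumb is a normal approximation and is too optimistic at four per group.

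At stake is how the result will be read. The article describes the trial as able to detect its target effect with 80 % power. If that is not so, readers will give a non-significant biomarker comparison more weight than it can bear.

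**Working it through.** **Inputs, all from *Statistical analysis*:** two-sided α = 0.05; power 0.80; d = 2 in SD units; ischemia rate p = 0.20; 20 per group before and 24 after the addition. The analysis text prints α with a percent sign. That conflicts with the power analysis and is a separate matter; 0.05 is used here.

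**1. The plan's own figure.** 16/2² = 4; 4 × 5 = 20; 20 × 1.2 = 24; 24 × 2 = 48. The arithmetic reproduces. With 4 per group the normal approximation gives 80.7 % power.

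**2. Step 1 with the planned t test.** Noncentral t, d = 2:

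| n per group | Power |
|---|---|
| 4 | 65.7 % |
| 5 | 79.1 % |
| 6 | 87.6 % |

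This figure applies only if a comparison of about 4 with 4 is actually run, that is, in ischemic patients only.

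**3. Step 2 with the stated whole-group comparison.** Assumptions, which are mine and not stated in the article: no RIPC effect in non-ischemic patients, and a constant SD.

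- Diluted difference: 0.2 × 2 SD = 0.4 SD.
- t test power at 0.4 SD: 23.4 % with 20 per group, 27.4 % with 24.
- The article's formula: 16/0.4² = 100 per group. Equivalently 4/p² = 4/0.04 = 100, where the plan has 4/p = 4/0.2 = 20. The exact t test calculation gives 99.1, so 100.
- Variant: if ischemic controls are shifted by 2 SD and RIPC protects fully, the mixture also raises the variance. The pooled SD is √((1 + 0.2 × 0.8 × 4 + 1)/2) = 1.149, the standardised difference is 0.4/1.149 = 0.348, and power is about 18–22 %.

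**4. The other reading: analysis by ischemia status.** The number of ischemic patients per arm is random (binomial, p = 0.2).

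| | 20 per group | 24 per group |
|---|---|---|
| Probability of at least 4 ischemic patients in both arms | 0.589² = 35 % | 0.736² = 54 % |
| t test in ischemic patients only, power averaged over the counts | 57 % | 68 % |
| Model with group, ischemia status and pooled variance, contrast in ischemic patients, averaged over the counts | 70 % | 79 % |

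The article specifies neither of these two analyses. Ischemia status is also observed after randomisation, so randomisation does not protect a comparison confined to ischemic patients.

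**5. Dependence on the ischemia rate.** The section on why RIPC is studied in unruptured aneurysms cites silent ischemia as high as 60 % in endovascular procedures. At p = 0.6 the diluted difference is 0.6 × 2 = 1.2 SD. Whole-group t test power is then 96 % (20 per group) to 98 % (24 per group) with constant SD, or about 86–92 % with the mixture variance.

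**6. What 20 to 24 evaluable patients per group do deliver.**

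- Difference detectable with 80 % power: 0.91 SD (20) or 0.83 SD (24).
- 95 % CI half-width, t × √(2/n): 2.024 × √(2/20) = 0.64 SD; 2.013 × √(2/24) = 0.58 SD.

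**The case against.** The best defence is the sentence naming intra-operative ischemia as the sole explanatory variable. Together with a sizing built to obtain four ischemic patients per arm, it suggests an analysis by ischemia status. On that reading dividing by p is the right scaling and nothing is diluted. This stands as a genuine ambiguity, so the 23–27 % must be given as conditional. It does not rescue the 80 %: the subset t test reaches 57–68 %, and the pooled-variance model comes close (79 %) only if all 24 per arm are retained.

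A second defence is that one in five is a cautious planning figure and that at 60 % the whole-group test is well powered. That is correct. But the authors sized the trial on one in five, and the shortfall follows from that input.

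Third, the trial is exploratory. A reader might infer that a null result would be taken as evidence against RIPC or would eliminate a biomarker. The article does not support that. Its *Discussion* says that planning after a non-significant primary result will rest on the full clinical, imaging and neuropsychological results, and that the trial will not be definitive. It also concedes that small effects might leave the study underpowered. These caveats soften the consequence. They do not correct the calculation, because the concession is about effects too small to detect, while here power is short for the planned effect itself.

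**Conclusion.** The stated 80 % power is wrong as written. For the intention-to-treat two-group t test it is about 23 % (20 per group) to 27 % (24 per group). That rests on no effect in non-ischemic patients, a constant SD and the article's one-in-five ischemia rate. For an analysis by ischemia status it is about 57–68 % or 70–79 %, depending on a model that the article does not specify. The four-per-group step alone gives 66 % with a t test.

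A reader might take 23–27 % as the trial's power without qualification. The document does not support that: the role of ischemia in the analysis is ambiguous, the zero-effect assumption is not stated in it, and a higher ischemia rate would change the answer substantially.

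**What to change.** Keep 48 patients and rewrite the sample-size paragraph:

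1. State that the whole-group intention-to-treat comparison of S100B AUC is primary, and reconcile the sentence on ischemia as sole explanatory variable with it.
2. Delete the claims that four per group gives 80 % power and that multiplying by five preserves it.
3. Insert text such as: *With 20 to 24 evaluable patients per group, a two-sided t test at the 0.05 level has 80 % power for a whole-group difference in S100B AUC of 0.91 to 0.83 SD, with a 95 % confidence interval half-width of 0.64 to 0.58 SD. If RIPC produces a 2 SD effect in one fifth of patients and none in the others, with constant SD, the group difference is 0.4 SD and power is about 23 to 27 %. Power rises with the ischemia rate. A non-significant result does not rule out the planned effect.*

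The cost is rewording only, with no extra patients or procedures. The downside is that the stated power becomes less favourable.
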